**Conclusions:**

We aim to develop a phenotypic description of women with endometriosis by linking the collected data with existing registry-based information on endometriosis diagnosis, healthcare utilization, and big data approach. This may help to achieve earlier detection of endometriosis with pelvic pain and significantly reduce the current diagnostic delay. Additionally, we may identify dietary components that worsen the quality of life and pain in women with endometriosis, upon which we can create real-world data-based nutritional recommendations.

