### Secondary objectives

To explore whether there is an association between removing or restricting dietary components and quality of life, pain, and central sensitization.To investigate the connections between different types of exercise, relaxation techniques, and the symptoms or diagnosis of individuals.To measure the financial implications of specific diets and different dietary supplements.

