### Questionnaire

Participants will be asked to complete a baseline questionnaire once and a longitudinal questionnaire monthly for one year. The questionnaire includes questions about endometriosis symptoms, socio-demographic information, mental and physical health, known medical conditions, medication use, dietary habits, economic burden, and lifestyle factors. These include free-text responses, single or multiple-choice questions, and numerical rating scales. See Supplementary Data for the questionnaires and https://hellolucy.app/en/ for the Lucy app.

Self-reported data of the participants will be measured as follows:

Evaluating the quality of life using the 5-level EQ-5D (EQ-5D-5L) and Endometriosis Health Profile 5 (EHP-5) [18].Assessing pain scores using the Visual Analogue Scale (VAS) [19].Examining somatic and emotional symptoms associated with central pain sensitization using the short version of the Central Sensitization Inventory (CSI-9) [20].

If using the same user account, Lucy app users can pause and resume completing the questionnaire, even on different devices. Once all questions have been answered, users can review and modify their answers on a summary screen. When they submit the questionnaire, their responses are stored on a server. At this point, the questionnaire’s content is fixed and cannot be changed.

In longitudinal studies, minimizing the drop-out rate and encouraging maximum user participation in completing the desired quantity of questionnaires is crucial. *Lucy app* users are anonymous; therefore, personal email contact is impossible. To address this challenge and reduce dropouts, the application uses several methods to notify users when the questionnaire becomes available for completion again. The questionnaire menu is prominently displayed on the application’s main page, and a pop-up window alerts users that the questionnaire is complete. Users can track the number of times and when they completed the questionnaire, but detailed completion data is not visible. The app displays a pop-up window with motivational quotes and positive messages to encourage and support users. In addition, users who complete the questionnaire are entered into a drawing as an additional incentive to participate. These measures are designed to minimize dropout and maximize user engagement in completing the questionnaires for the study.

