### Statistical and machine learning analyses

Our dataset comprises both diagnosed and undiagnosed patients, enabling us to evaluate the quality of the data. The goal is to have a case-control ratio of 1:1 in the dataset. Specifically, records from patients diagnosed with endometriosis but not yet received treatment should highly correlate with well-known endometriosis-associated symptoms, such as pelvic pain.

The normal distribution of the data will be tested with histograms and QQ-plots. Continuous variables will be presented as averages (mean ± SD), nominal variables as numbers (n) and percentages (%). A level of statistical significance of P < 0.05 will be used. The VAS scores of the endometriosis group and the reference group will be compared with independent sample t-tests. Also, independent samples t-tests will be conducted to see whether EQ-5D-5L, CSI-9 and EHP-5 scores were different between diet-users and non-diet users. Subsequently, a one-way analysis of variance of no diet use and the various diets will be carried out for the EQ-5D-5L, CSI-9, and EHP-5 scores. A post-hoc multiple comparisons analysis (Tukey honestly significant difference) will be used to identify where the differences between these diet groups were located. Preliminary analyses will involve various correlation techniques and visual representations, including heat maps contrasting diseases against symptoms.

To explore associations between diseases, symptoms, severity, dietary habits, and lifestyle activities, we will employ Cramér’s V statistical method. Additional validation of patient segmentation will be conducted to confirm that emerging patient cohorts exhibit anticipated symptoms. Machine learning algorithms will be deployed to uncover hidden relationships or patterns. Density-Based Spatial Clustering of Applications with Noise (DBSCAN) and Uniform Manifold Approximation and Projection (UMAP) will be employed to visualize high-dimensional symptom and activity spaces in 2D or 3D representations for dimensionality reduction and clustering. Risk assessments for undiagnosed patients will be computed using Random Forest and Long Short-Term Memory (LSTM) models. The LSTM models will fully leverage the time-series data, offering predictive insights into disease outcomes based on the temporal progression of symptoms.

All the methodologies above will be tested under various scenarios, such as:

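### Cramér's V has no sign and ignores order, so it cannot show whether exercise or relaxation goes with more or less severe symptoms, and no named signed analysis links diet to VAS pain

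*Protocol article*

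**What the plan says.** The Statistical and machine learning analyses section gives the aim "To explore associations between diseases, symptoms, severity, dietary habits, and lifestyle activities" and continues: "we will employ Cramér’s V statistical method". Severity is an ordered quantity, and exercise and relaxation belong to the lifestyle activities.

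The second secondary objective that this serves is "To investigate the connections between different types of exercise, relaxation techniques, and the symptoms or diagnosis of individuals". The first concerns diet: "To explore whether there is an association between removing or restricting dietary components and quality of life, pain, and central sensitization". The abstract's conclusions add a directional hope for diet: "we may identify dietary components that worsen the quality of life and pain in women with endometriosis".

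On response formats, the Questionnaire section says: "These include free-text responses, single or multiple-choice questions, and numerical rating scales". Pain is scored on a VAS.

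The same statistical section plans other analyses that do give direction, but for other comparisons:
- For diet, "independent samples t-tests will be conducted to see whether EQ-5D-5L, CSI-9 and EHP-5 scores were different between diet-users and non-diet users", followed by a one-way ANOVA across diets with Tukey comparisons on the same three scores.
- For VAS, a t-test between the endometriosis group and the reference group only.
- Correlation techniques that are not named, described as preliminary and illustrated by heat maps of diseases against symptoms.

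**The concern.** Cramér's V measures how far a cross-table departs from independence. It suits two nominal variables. When one variable is ordered, V discards the order, and it never has a direction.

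The objective on exercise and relaxation is of little use without direction. A patient or clinician wants to know whether an activity goes with milder or worse symptoms. If the result is a V, the reader learns that the two are related and how strongly, but not which way. The same applies to diet and pain: the article hopes to find components that make pain worse, yet no named analysis gives a signed comparison of VAS by diet.

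A lesser issue is efficiency. The chi-square statistic behind V spreads a monotone trend over several degrees of freedom, so a test based on it is weaker than a one-degree-of-freedom trend test.

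**Working it through.** The article gives no effect size, category count or power for this analysis, so there is no figure to reproduce. All tables below are assumptions made to show how the statistic behaves.

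**1. Which named analysis covers which question**

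| Question | Named signed analysis | Cramér's V |
|---|---|---|
| Diet vs EQ-5D-5L, CSI-9, EHP-5 | t-test, ANOVA/Tukey | dietary habits listed |
| Diet vs VAS pain | none | dietary habits listed |
| Exercise or relaxation vs symptom severity | none | lifestyle activities and severity listed |
| Endometriosis vs reference, VAS | t-test | not needed |

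**2. Direction**

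Assumed table, 2,500 women per group, severity none / mild / moderate / severe:
- non-exercisers: 500 / 600 / 700 / 700
- exercisers: 700 / 700 / 600 / 500

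The column totals are 1,200, 1,300, 1,300 and 1,200, so the expected count in each row is 600, 650, 650 and 600.

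Chi-square = 2 × (100²/600 + 50²/650 + 50²/650 + 100²/600) = 2 × 41.03 = 82.05.

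V = sqrt(chi-square / (n × (min(r, c) − 1))) = sqrt(82.05 / (5,000 × 1)) = 0.128.

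Kendall's tau-b on the same table: concordant pairs 1,910,000, discordant pairs 2,800,000, difference −890,000. Pairs not tied on group: 2,500 × 2,500 = 6,250,000. Pairs not tied on severity: 12,497,500 − 3,127,500 = 9,370,000. tau-b = −890,000 / sqrt(6,250,000 × 9,370,000) = −0.116. Spearman's rho is −0.127. With severity scored 0 to 3, the group means are 3,400/2,500 = 1.36 and 4,100/2,500 = 1.64, a difference of −0.28 categories.

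Now swap the two rows, so that exercise goes with worse symptoms:

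| | V | rho | tau-b | mean difference |
|---|---|---|---|---|
| Exercisers less severe | 0.128 | −0.127 | −0.116 | −0.28 |
| Exercisers more severe | 0.128 | +0.127 | +0.116 | +0.28 |

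V is the same in both rows of this table; the other three change sign.

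**3. Order**

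Relabelling the four severity levels in all 24 possible orders leaves V at 0.128 each time, while rho ranges from −0.127 to +0.127. V makes no use of the fact that severe is worse than mild.

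**4. Power cost of ignoring order**

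Assume the whole signal is a linear trend and alpha is 0.05. The noncentrality needed for 80% power is 7.85 for a one-df trend test. For the general chi-square:

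| df (example table) | Noncentrality for 80% | Sample ratio to trend test | Power when trend test has 80% |
|---|---|---|---|
| 3 (2×4) | 10.90 | 10.90/7.85 = 1.39 | 64% |
| 4 (2×5) | 11.94 | 1.52 | 60% |
| 16 (5×5) | 19.27 | 2.45 | 34% |
| 40 (5×11) | 27.56 | 3.51 | 22% |

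As a concrete case, take a small assumed shift from 25/25/25/25% to 28/26/24/22% in two equal groups. At N = 1,000 the chi-square test has 19% power and the trend test 29%. At N = 5,000 the figures are 76% and 89%. At N = 10,000 the chi-square noncentrality is 2 × 10.03 = 20.07, well above the 10.90 needed for 80% power on 3 df.

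**The case against.** **V is the right tool for much of what the sentence covers.** Exercise type, relaxation technique and diagnosis are nominal, and V suits nominal pairs. This stands, and the fix keeps V there. A reader might infer that V is wrong throughout; it is not.

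**Diet has signed analyses.** A reader might infer that the plan cannot see direction for diet at all. It can: the t-tests and ANOVA/Tukey give signed differences for EQ-5D-5L, EHP-5 and CSI-9, and the last of these is itself a symptom inventory. The diet gap among the named signed analyses that matters here is VAS pain.

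**The work is exploratory, and direction may emerge elsewhere.** The objective speaks of connections, the unnamed correlation techniques could include rank correlations, and counts and percentages reported by group would show direction. This is fair, and it limits the point. But the correlations are preliminary and illustrated only for diseases against symptoms, and the article does not commit to reading direction from cross-tables. V is what it does commit to, for a list that includes severity.

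**Nothing says that VAS or rating scales will be cut into categories for V.** This is correct, and the documents do not support claiming it. The ordinal complaint rests on severity being in V's list. For VAS, the complaint is that no named signed comparison links it to diet, exercise or relaxation.

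**The power loss can be made to look large.** The 16-df and 40-df tables appear nowhere in the article, and with four or five severity levels by a yes/no activity the sample ratio is only about 1.4 to 1.5. Power is not the limit at the planned size.

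**Covariate adjustment is a detail for the full plan.** This is agreed. Its absence from an article is not an error, and the article does plan to segment by diagnosed versus undiagnosed.

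**Conclusion.** The point holds in a limited form. The article commits to an unsigned, order-blind statistic for associations that include severity and lifestyle activities, and names no other association statistic for the exercise and relaxation objective. For ordered outcomes, V alone cannot tell benefit from harm: 0.128 in both directions in the assumed table, against −0.127 and +0.127 for rho. For diet the gap is narrower, namely the lack of a named signed analysis of VAS pain.

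That V has no direction is a mathematical property and does not depend on sample size or on the assumed table. The power cost does depend on assumptions (a purely linear trend, and a sample ratio of about 1.4 at 3 df, 2.5 at 16 df and 3.5 at 40 df). It is secondary at 10,000 participants and could matter only in small subgroups, which the article does not size.

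**What to change.** 1. Restrict Cramér's V to pairs of nominal variables, such as exercise type by diagnosis.
2. Where one variable is ordered or numeric (severity, VAS, rating scales), report a signed, order-using estimate with a 95% CI. Use Spearman's rho or Kendall's tau-b for ordered pairs. For a yes/no or nominal activity, use a group mean difference or an ordinal or linear regression coefficient.
3. Name one such estimate as the analysis for the exercise and relaxation objective.
4. Add VAS to the scores in the planned diet t-tests and ANOVA/Tukey comparisons.

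Adjustment for collected covariates such as age and diagnosis group is optional. Country should not be assumed available as a covariate, because the article lists the countries but does not describe country as a participant-level variable.

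The cost is a wording change, a few lines of code and slightly longer reporting. The symptom, pain and activity data that the plan already intends to analyse are sufficient; rank correlation for an activity also needs an ordered measure of it, such as frequency, which the article text does not document.

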## Introduction

Endometriosis is a chronic inflammatory disease with endometrium-like tissue outside the uterine cavity [1, 2]. It is commonly associated with chronic pelvic pain, infertility, and decreased quality of life, although asymptomatic cases exist [3–5]. The exact prevalence of endometriosis is unknown, but it may affect 5–10% of women and those assigned female at birth during their reproductive years, which equals nearly 190 million people worldwide [1]. Despite this high prevalence, recognition of the disease is inadequate, underprioritized, and research is underfunded, contributing to diagnostic delays ranging from 4 to 11 years [6–9]. Accordingly, endometriosis should be considered a public health issue, and reducing the current diagnostic delay is paramount.

Lucy is a mobile health application (Lucy app) designed to alert users with an increased risk of endometriosis to seek medical attention. Users can input their menstrual cycle information, health status, medical records or diagnoses, dietary details, lifestyle, and pain symptoms. Specialists in reproductive gynecology and health psychologists developed the app’s algorithm to continuously analyze the recorded data and alert the user when the entered symptoms are strongly associated with endometriosis.

A baseline questionnaire and a longitudinal questionnaire were developed and implemented as an additional module in the Lucy app. It collects self-reported data on symptoms of endometriosis, socio-demographics, mental and physical health, economic factors, nutrition, and other lifestyle factors [10]. By linking the collected information with existing registry-based information on diagnoses of endometriosis, healthcare use, and the big data approach, we can develop a phenotype description of individuals with endometriosis and structured clinical data [11].

So far, only one study has investigated this question with big data analysis using machine learning (ML). According to Bendifallah *et al*., endometriosis can generally be diagnosed with high diagnostic accuracy based on endometriosis-related symptoms and demographic data using ML technology [12]. The work presented by these authors was based on medical records of 800 participants of a French cohort and not on patient self-reported data.

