### Eligibility criteria

5,000 women with confirmed endometriosis and 5,000 women without diagnosed endometriosis in a control group aged 18–45 years will be enrolled and followed up for one year.

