Including all available symptoms and lifestyle/dietary activities.Excluding variables considered irrelevant based on existing medical literature.Segmenting the analysis for diagnosed versus undiagnosed patients.

These tests will help validate whether the methodologies yield consistent and reliable results. Given the substantial volume of our dataset—exceeding a million patient records—the data should be sufficient to use novel Transformer network models for pattern recognition and predictive analytics for at least low-complexity cases.

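### Cramér's V varies with the case share, which the design aims to set at 50% against 5–10% in the population, so pooled values do not carry over to the population

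*Protocol article*

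**What the plan says.** The section on statistical and machine learning analyses names one association measure for the exploratory part: "To explore associations between diseases, symptoms, severity, dietary habits, and lifestyle activities, we will employ Cramér’s V statistical method". The same section sets the composition of the data: "The goal is to have a case-control ratio of 1:1 in the dataset". The eligibility criteria give the numbers: "5,000 women with confirmed endometriosis and 5,000 women without diagnosed endometriosis in a control group aged 18–45 years will be enrolled". On frequency in the population, the Introduction says of endometriosis that "it may affect 5–10% of women and those assigned female at birth during their reproductive years", and calls the exact figure unknown.

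One secondary objective that such an analysis would serve is "To investigate the connections between different types of exercise, relaxation techniques, and the symptoms or diagnosis of individuals". The general significance rule is "A level of statistical significance of P < 0.05 will be used".

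The section ends with alternative runs. It introduces them with "All the methodologies above will be tested under various scenarios, such as", and one of those listed is "Segmenting the analysis for diagnosed versus undiagnosed patients". They are presented as a test of whether the methods give consistent and reliable results. The article names neither an odds ratio nor a weighting to population prevalence.

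**The concern.** Cramér's V is not a property of the two variables alone. It also depends on how common each category is in the table, and here recruitment determines how common the diagnosis is. Two consequences follow.

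- **Pairs that involve the diagnosis** (endometriosis with a symptom, or with exercise, relaxation or diet). The same symptom frequencies in affected and unaffected women give a different V at a 50% case share than at 5–10%.
- **Pairs that do not involve the diagnosis** (a lifestyle factor with a symptom). If both variables are related to endometriosis, over-representing cases strengthens the link that runs through disease. It can also produce a link that the population does not have.

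At stake is how the association results will be read. The study's stated purpose is real-world patterns and real-world dietary advice. A pooled V from a balanced sample would be hard to compare with other cohorts. With 10,000 women, a small value made by sampling would also pass the 5% level.

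**Working it through.** **Inputs from the protocol.** 5,000 cases and 5,000 controls, so the target case share is 5,000/10,000 = 50%, which agrees with the stated 1:1 ratio. Prevalence 5–10%. Significance level 0.05. The protocol gives no value of V to reproduce.

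**Inputs assumed here.** All symptom and lifestyle frequencies and all odds ratios with disease. They are illustrations, not estimates.

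**Step 1: diagnosis against a symptom.** For a 2×2 table, V = |a − b|·√[p(1−p)] / √[m(1−m)], where p is the case share, a and b are the symptom frequencies in cases and controls, and m = pa + (1−p)b. With a = 0.80 and b = 0.30:

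| Case share p | m | √[p(1−p)] | V |
|---|---|---|---|
| 50% | 0.550 | 0.500 | 0.503 |
| 10% | 0.350 | 0.300 | 0.314 |
| 5% | 0.325 | 0.218 | 0.233 |

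The odds ratio is (0.8/0.2)/(0.3/0.7) = 9.33 in every row.

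Other assumed frequencies, V at 5% / 10% / 50%:
- 70% vs 30%: 0.187 / 0.253 / 0.400
- 50% vs 20%: 0.159 / 0.214 / 0.314
- 30% vs 10%: 0.139 / 0.185 / 0.250
- 30% vs 1%: 0.409 / 0.449 / 0.401, where V at 1:1 is the lowest of the three

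Over all pairs a > b on a 1%–99% grid, the median ratio of V at 50% to V at 10% is 1.61, and to V at 5% it is 2.19. V is lower at 50% in 2.8% and 1.0% of the grid respectively. These are cases where the symptom is almost absent in controls, or the mirror image.

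Segmenting by diagnosis cannot help these pairs. Within a segment the diagnosis is constant, so the table has no V.

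**Step 2: lifestyle against a symptom, unrelated within each group.** Symptom as in step 1; exercise 30% in cases and 50% in controls. The pooled value is phi = p(1−p)(a₁−b₁)(a₂−b₂) / √[m₁(1−m₁)m₂(1−m₂)], and V is its absolute value.

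- p = 50%: 0.25 × 0.5 × (−0.2) / 0.2437 = −0.103, so V = 0.103; chi-square = 10,000 × 0.1026² ≈ 105
- p = 10%: 0.09 × 0.5 × (−0.2) / 0.2383 = −0.038, so V = 0.038
- p = 5%: 0.0475 × 0.5 × (−0.2) / 0.2341 = −0.020, so V = 0.020

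The population V is not 0 here, because disease links the two variables. The 1:1 ratio multiplies it by about 2.7 (0.103/0.038) to 5 (0.103/0.020). Within cases and within controls V is 0.

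**Step 3: lifestyle against a symptom, unrelated in the population.** Both at 30% and independent, so population V = 0. Each raises the odds of disease on a logistic scale, by 3 (lifestyle) and 5 (symptom).

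At 5% prevalence the disease risks are 1.56% (neither), 4.55% (lifestyle only), 7.36% (symptom only) and 19.25% (both). Check: 0.49 × 0.0156 + 0.21 × 0.0455 + 0.21 × 0.0736 + 0.09 × 0.1925 = 0.050.

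- Both present: 0.09 × 0.1925/0.05 = 0.3465 of cases and 0.09 × 0.8075/0.95 = 0.0765 of controls, mean 0.2115
- Lifestyle factor: 0.5376 of cases and 0.2875 of controls, mean 0.4125
- Symptom: 0.6556 of cases and 0.2813 of controls, mean 0.4684
- Pooled 1:1 V = (0.2115 − 0.4125 × 0.4684) / √(0.4125 × 0.5875 × 0.4684 × 0.5316) = 0.074, chi-square 55

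The same steps at 10% prevalence give V = 0.051, chi-square 26. With odds ratios of 2 and 2, V is 0.021 (5%) or 0.015 (10%). The 5% threshold at N = 10,000 is 1.96/√10,000 = 0.0196.

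Segmenting does not return exactly 0 in the example with 3 and 5. It leaves an absolute V of 0.025 (cases) and 0.021 (controls) at 5% prevalence, and 0.048 and 0.038 at 10%.

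**The case against.** The strongest reply is that the analysis is exploratory. The protocol nowhere says that V estimates a population strength, sets no cut-off for V and ties no decision to it. V in a balanced sample correctly describes that sample. The 1:1 ratio is a goal, only the endometriosis margin is shaped by it, and other correlation techniques, heat maps, clustering and prediction models are planned beside V. The scenarios also apply to every method listed, so V will be computed within diagnosed and within undiagnosed women anyway. For lifestyle–symptom pairs, what is open is which panel is reported.

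Most of this stands, and it rules out three stronger readings.

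- **That 1:1 sampling always inflates V.** It does not: at 30% vs 1%, V falls from 0.449 (10% share) to 0.401 (50%).
- **That pooled lifestyle–symptom values are simply made by the sampling.** In step 2 the association already exists in the population and is amplified. Creation from 0 occurs only in settings such as step 3, and the values are small.
- **That the protocol passes V off as a population figure, or ignores stratification.** The documents support neither; segmentation is listed.

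The reply does not reach pairs that involve the diagnosis, since segmentation removes the variable of interest. For the other pairs it leaves the segmented run as a consistency check and does not make it the result.

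**Conclusion.** The point holds in limited form. The protocol combines a measure that depends on the margins with a margin that the design aims to set at 50%, against its own figure of 5–10%. For pairs with the endometriosis diagnosis, V will usually be larger than in the population: 0.50 against 0.23–0.31 in the main example, and typically about 1.6 to 2.2 times larger on the grid. For other pairs, pooling amplifies an association through disease (0.10 against 0.02–0.04), or creates one of about 0.05–0.07 where there is none in the population. These are weak associations, but detectable with 10,000 women.

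The sizes rest on assumed frequencies and odds ratios, and on the 1:1 goal being met. Controls are women without a diagnosis, so some may have undiagnosed disease, which would lower V for diagnosis pairs. The matter concerns reporting of an exploratory analysis and does not invalidate the study. It is worth correcting because the shift is systematic and the remedy cheap.

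**What to change.** 1. For pairs that involve the endometriosis diagnosis, report odds ratios with 95% confidence intervals, which do not change with the case-control ratio. Keep V, if wanted, only as a description of this sample, and say so.
2. For lifestyle–symptom and diet–symptom pairs, make the analysis segmented by diagnosis, already in the list of scenarios, the reported result in place of the pooled 1:1 V.
3. If a population-level association is wanted, report an estimate weighted to 5–10% prevalence as a separate, labelled quantity. It is not interchangeable with the segmented one. In step 2 weighting gives 0.020–0.038 where segmentation gives 0. In step 3 weighting to the true prevalence returns 0 where segmentation leaves about 0.02–0.05. The text should say which question each answers.

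This changes analysis wording only and needs no new data. The downside is two panels instead of one, about 5,000 women per panel instead of 10,000, and smaller headline values.

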No evidence-based advice concerning effective dietary interventions can be given to women with endometriosis [13]. Specifically, the effect of red meat, sugar, soy, dairy products, gluten, and caffeine on symptoms in women with endometriosis has not yet been systematically recorded. Therefore, we aim to investigate the effects of dietary restriction of these components on changes in quality of life, pain, and central pain sensitization. With this information, we may be able to identify nutritional components that affect the quality of life and pain in women with endometriosis. Consequently, real-world data-based dietary recommendations could be generated.

The present study aims to investigate the association between self-reported data and the clinical presentation of endometriosis. This could contribute to the classification of novel etiologic endometriosis. Such etiological findings could help to identify patterns that may categorize novel clinical subgroups of the disease. In addition, developing patient profiles may provide a novel diagnostic tool for the non-invasive, early detection of endometriosis.

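### Patient clusters formed largely from symptoms are validated by whether they show the expected symptoms, which is partly circular and favours known phenotypes over the novel subgroups sought

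*Protocol article*

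**What the plan says.** All of the following is in the protocol article.

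- **Forming the clusters.** Under Statistical and machine learning analyses, DBSCAN and UMAP "will be employed to visualize high-dimensional symptom and activity spaces in 2D or 3D representations for dimensionality reduction and clustering".
- **Validating them.** The same section says: "Additional validation of patient segmentation will be conducted to confirm that emerging patient cohorts exhibit anticipated symptoms". It gives no threshold, and no consequence if a cohort does not meet the expectation.
- **What the clusters are for.** The Introduction hopes to "identify patterns that may categorize novel clinical subgroups of the disease". The primary objective is to find distinct clinical cohorts, and the Conclusions section repeats the aim of new subgroups. The analysis section adds: "Machine learning algorithms will be deployed to uncover hidden relationships or patterns".
- **Atypical disease is accepted.** The Introduction describes endometriosis as commonly linked to pelvic pain, "although asymptomatic cases exist".
- **Other checks.** The analysis section closes with scenarios in which the methods are rerun: with all variables, without those the literature deems irrelevant, and split by diagnosis status. Their purpose is to see whether results are consistent.

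**The concern.** A validation step should be able to separate a real subgroup from an artefact of the algorithm. Checking clusters on variables of the kind that built them does this poorly, because an algorithm that groups women by symptoms yields groups with different symptom profiles whether or not the population contains subgroups.

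The criterion also has a direction. Asking for the symptoms that were anticipated rewards clusters that restate what is already known. A stable cluster with few or unusual symptoms would be the most interesting result for the stated aim, and it gains nothing from this check.

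The primary objective is at stake, since the patient profiles meant to support earlier detection depend on the cohorts being real.

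**Working it through.** **No figure to reproduce.** The article gives no threshold, error rate or power for this step. The argument rests on the text; the simulations below only illustrate it, on assumed inputs.

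**Text side by side.** The clustering inputs are symptoms and activities. The validating variables are symptoms. The two sets overlap. The scenarios at the end of the section change the variable set or split the women by diagnosis, but they reuse the same data and name no held-out sample or outside variable. One scenario removes variables on the strength of existing literature, which leans further towards what is known.

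**Illustration A: reuse of clustering variables when nothing is there.**
- Assumed: 2,000 women, 10 independent binary symptoms, each with prevalence 0.40, k-means with 3 clusters, 200 runs. One further independent binary variable is kept out of the clustering.
- Check on the clustering symptoms: smallest of 10 chi-square p-values below 0.05/10 = 0.005. Met in 200 of 200 runs (100%).
- Check on the kept-out variable: chi-square p < 0.05. Met in 7 of 200 runs (3.5%). The Monte Carlo standard error at a true 5% is √(0.05 × 0.95 / 200) = 0.0154, so 3.5% is about one standard error from nominal.
- A continuous version (5,000 women, 20 independent normal variables, 4 k-means clusters, 50 runs) agrees: 99.6% of the clustering variables differed between clusters at p < 0.05.

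**What A does not show.** It asks whether symptoms differ in any direction. The stated check asks whether anticipated symptoms are present. In noise of the continuous kind, one designated symptom was significantly raised in about 39% to 46% of clusters, and never in all four clusters of a run. At least one of five designated symptoms was raised in about 95% of clusters, and at least three of five in about 35%. How easily noise passes therefore depends on how many anticipated symptoms are required, which the article does not state.

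**Illustration B: the lean towards known phenotypes.**
- Assumed: a real subgroup of 500 against 5,000 controls, pelvic-pain prevalence 0.40 in controls. Suppose, although the article does not say so, that a subgroup passes when its prevalence q is significantly above control.
- Statistic: z = (q − 0.40) / √(q(1 − q)/500 + 0.40 × 0.60/5000), pass if z > 1.96.

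| q in subgroup | z at the true values | share passing |
|---|---|---|
| 0.20 | −0.20/√(0.000320 + 0.000048) = −10.4 | 0% |
| 0.40 | 0 | 2.4% |
| 0.60 | 0.20/√(0.000480 + 0.000048) = 8.7 | 100% |
| 0.70 | 0.30/√(0.000420 + 0.000048) = 13.9 | 100% |

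All four subgroups are real. Under such a rule, what decides is resemblance to the known picture.

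**The case against.** **No rejection rule.** A reader might infer that novel subgroups would be rejected. The article does not support that. It states no gate and no discard step, and a new subgroup may share pelvic pain while differing in comorbidity, severity or lifestyle, all of which the primary objective lists. This stands, and it limits the point to a risk.

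**The simulations use another algorithm and another test.** K-means always returns the requested number of clusters; DBSCAN need not. In a trial on 2,000 × 20 Gaussian noise, DBSCAN alone gave no cluster or a single one in 11 of 12 settings. UMAP followed by DBSCAN was not tested. This also stands: neither 99.6% nor 100% is the pass rate of the planned check. It does not make symptoms an independent criterion for clusters that DBSCAN/UMAP builds from symptoms.

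**Data quality.** A reader might extend the charge to the sentence that diagnosed, untreated records "should highly correlate with well-known endometriosis-associated symptoms, such as pelvic pain". That does not hold. It is a reasonable known-groups check at group level, and the existence of some asymptomatic cases does not contradict it. The exclusions listed under Data quality assessment and preprocessing do not use diagnosis, and nothing ties filtering to this correlation.

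**It is not the only validation.** The sentence calls the check additional, and scenario reruns follow. True, but those reruns are internal to the same data.

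**The reading is an inference.** The sentence stands just before those on machine learning, and segmentation could mean diagnosed versus undiagnosed. But cohorts that emerge are a product of clustering, and the primary objective is to identify cohorts. The clustering reading is the more natural one.

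**An article may leave methods to a fuller plan.** Agreed for unstated detail. Here a weak criterion is stated, and the point is to replace it.

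**Conclusion.** The point holds as a weakness in a stated criterion and should be addressed before the cluster analysis. Agreement with anticipated symptoms is partly circular for groups formed in symptom space, and it pulls against the search for novel subgroups. The likely harm is that artefacts appear confirmed and atypical clusters stay unvalidated.

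The size for this study cannot be computed, because the article fixes neither the list of anticipated symptoms nor a pass rule. The contrast of 100% with 3.5% illustrates the effect of reusing variables. It assumes k-means, independent symptoms and a kept-out variable unrelated to them. The conclusion itself rests on two readings of the text: that segmentation refers to the clusters, and that symptoms enter the clustering, which the section states.

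**What to change.** Describe the symptom check as a description of clinical plausibility, not as validation. Base cluster validity on:

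1. stability under bootstrap or split-sample resampling, for example by the Jaccard or adjusted Rand index;
2. reproduction in a held-out country (eight are listed under Study design) or a held-out recruitment period;
3. differences on variables kept out of the clustering, such as EQ-5D-5L, EHP-5 or the registry data that the study plans to link.

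The third item should not stand alone. A smooth severity gradient cut into groups would also differ on quality of life, so stability and reproduction are needed beside it.

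Report stable clusters with unexpected symptoms as candidate subgroups.

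Cost: a change of wording, routine resampling code, and a few variables withheld from the clustering. The questionnaire measures are already collected and the linkage is already planned, so no new data collection is needed.
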